#### Study objectives

To determine if WBV in addition to standard PTH 1-34 treatment has a greater effect in osteoporotic patients compared to standard PTH 1-34 treatment alone on:BMDBone microarchitectureMarkers of bone formation and resorptionMuscle function and balanceTo assess the safety and adherence to WBV in osteoporotic patients

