## Methods/design

### General design

This will be a multicenter, assessor-blinded, superiority, two-armed RCT in osteoporotic patients starting standard PTH 1-34 treatment. In Denmark, PTH 1-34 is used for the treatment of severe osteoporosis, and the cost is reimbursed if patients have a lumbar spine or total hip T-score ≤ − 3 combined with at least one clinical vertebral fracture (compression ≥ 25%) within the past 3 years or at least two vertebral fractures (compression ≥ 25%) independently of BMD. Participants will be randomized to PTH 1-34 treatment alone or to combined PTH 1-34 treatment and WBV (see Fig. 1). The study will be reported according to the Consolidated Standards of Reporting Trials (CONSORT) extension to non-pharmaceutical interventions and the Standard Protocol Items: Recommendations for Interventional Trials (SPIRIT) 2013 Checklist for RCTs (Additional file 1).

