### Randomization

After informed consent and collection of baseline data, participants will be randomized into two groups: PTH 1-34 treatment alone or PTH 1-34 treatment + WBV (Fig. 2). The randomization is a web-based, computer-generated block randomization with no stratification. Block size is created by a data manager and the size is unknown to the investigators until the end of the study. Allocation will be concealed to the participants and the investigators until after collection of baseline data.

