#### Statistical methods and data managing

The intervention arm (PTH + WBV) is compared against the control arm for all primary analyses. We will use analysis of covariance (ANCOVA) and “percentage change” for primary outcome adjusting for baseline measurements. For secondary outcomes we will use a chi-squared test for binary outcomes, analysis of variance (ANOVA) and the *T* test for continuous outcomes, and for non-normally distributed continuous outcomes we will use log transformation or Wilcoxon’s match-pairs signed-rank test and the Kruskal-Wallis test.

All *p* values will be reported to four decimal places with *p* values < 0.001 reported as *p* < 0.001. STATA version 14 will be used to conduct analyses. For all tests, we will use two-sided *p* values with an alpha ≤ 0.05 level of significance.

The analyses will be conducted with the intention-to-treat method, and in order to investigate the effect of adherence and withdrawal a per-protocol analysis will be conducted. Missing data will be handled using multiple imputation. Study data is collected and managed using REDCap (Version 6.5.10 – © 2015 Vanderbilt University) electronic data capture tools hosted at the University of Southern Denmark [44]. Sequential study numbers will be allocated to study patients and entered into the recruitment log at the secure web database REDCap.

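### One of the two rank tests named for non-normal secondary outcomes is a paired test that cannot compare the randomised arms, and the text does not say which test serves which comparison

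*Protocol article*

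**What the plan says.** All places are in the protocol article.

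- **Statistical methods and data managing.** Binary secondary outcomes get a chi-squared test, and continuous ones get ANOVA and the t test. Where normality fails, the choice is log transformation or the Wilcoxon "match-pairs signed-rank test and the Kruskal-Wallis test". The sentence does not say which procedure goes with which comparison. The nearest statement is "The intervention arm (PTH + WBV) is compared against the control arm for all primary analyses", and it speaks only of the primary analyses.
- **General design.** "This will be a multicenter, assessor-blinded, superiority, two-armed RCT in osteoporotic patients starting standard PTH 1-34 treatment".
- **Randomization.** "The randomization is a web-based, computer-generated block randomization with no stratification". Nothing in the article matches a woman in one arm to a woman in the other.
- **Study objectives.** The question is whether adding WBV "has a greater effect in osteoporotic patients compared to standard PTH 1-34 treatment alone", for bone microarchitecture, bone markers and muscle function as well as BMD.
- **Endpoints, Table 2.** Most secondary endpoints are changes from baseline, at up to five follow-up times.
- **Randomization, text with Fig. 2.** After 12 months the WBV arm is split at random into women who continue and women who stop, which gives three groups in the second year.

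**The concern.** In the sentence on secondary outcomes, the signed-rank test stands where the rank counterpart of the two-sample t test would be expected. That counterpart is the Wilcoxon rank-sum (Mann-Whitney) test. The two tests share a name but answer different questions. The signed-rank test needs a natural pair for each observation, and the rank-sum test compares two independent groups. The article spells out the matched-pairs form, so this is not a shorthand that a reader would safely take as rank-sum.

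An analyst who follows the sentence could test each arm's follow-up against its own baseline and report two p values. Because most secondary endpoints are already changes from baseline, this is an easy step to take. A result that is significant with WBV and not significant without it may then be read as an effect of WBV, although the arms were never compared.

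**Working it through.** **1. Can the named tests answer the between-arm question?**

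| Procedure named | Data it needs | Compares the two arms? |
|---|---|---|
| Log transformation, then t test or ANOVA | independent groups | yes |
| Wilcoxon matched-pairs signed-rank | pairs | no: no pairs exist across arms |
| Kruskal-Wallis | two or more independent groups | yes |

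So one of the two rank tests is unsuited to the comparison that the objectives set, and the other is suited.

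**2. Is Kruskal-Wallis enough with two arms?** With two groups it is the rank-sum test in another form. In 500 simulated skewed (log-normal) data sets with 16 per arm, the two p values differed by at most 5e-14 (no continuity correction). The article therefore already contains a valid between-arm rank test.

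**3. The sample size, to fix the number per arm.** The inputs come from the sample size section: difference 11% − 9% = 2 points, SD 2%, two-sided alpha 0.05, power 80%.

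n per arm = 2 × (1.96 + 0.84)² × 2² / 2² = 15.7, rounded up to 16. With 20% dropout, 32 / 0.8 = 40.

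Both agree with the article. Nothing in this point changes them. The figure of 16 per arm is used below only as a realistic size.

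**4. What two within-arm tests would show if WBV added nothing.** The assumptions are mine and not the article's: normal changes, the same mean change d (in SD units) in both arms, 16 per arm, alpha 0.05, and 4,000 simulated trials for each d. If each arm is significant with probability p, the arms disagree with probability 2p(1 − p).

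| d | p per arm (simulated) | 2p(1 − p) | Disagreement (simulated) |
|---|---|---|---|
| 0.3 | 0.18 | 2 × 0.18 × 0.82 = 0.30 | 0.29 |
| 0.5 | 0.42 | 2 × 0.42 × 0.58 = 0.49 | 0.49 |
| 0.7 | 0.70 | 2 × 0.70 × 0.30 = 0.42 | 0.42 |
| 0.9 | 0.90 | 2 × 0.90 × 0.10 = 0.18 | 0.18 |

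Over the same scenarios the between-arm rank-sum test rejected in 4.3% to 5.2% of trials. Independent repeats of the simulation gave 29/50/41/19% and about 30/49/43/18%. The formula holds for any distribution; only p depends on the normal assumption.

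**5. A larger common change.** At d = 1 with no difference between arms, the signed-rank test within one arm rejects in 95% of trials and Kruskal-Wallis between arms in 4.7%. The within-arm test is then almost always significant and says nothing about WBV.

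**The case against.** **The plan already holds a valid test.** The same sentence names Kruskal-Wallis, and it lists log transformation ahead of both rank tests. This stands. A reader might infer that the secondary outcomes have no usable between-arm rank test, and the article does not support that. What remains is that an unsuited test is named next to a suited one, with no rule for choosing between them.

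**A paired test may have a proper use.** The second year asks whether gains wear off or persist after WBV stops. This could be examined as a change from 12 to 24 months in the same women. The article does not exclude this use, but it does not state it either, and it sets no such limit on the test.

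**The simulated disagreement is not an error rate of the plan.** This also stands. The 18% to 50% become false claims only if someone reads significance in one arm alone as a WBV effect, and the article nowhere proposes that inference. The simulated changes are also normal, whereas the rule applies to non-normal outcomes.

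**Arm sizes may stay equal.** Intention to treat with multiple imputation could keep the arms at their randomised sizes, so unequal numbers after dropout are not established. The point does not need them, because independent arms of equal size are still unpaired.

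**A condensed article may leave the assignment of tests to the analysis plan.** That would excuse silence. It does not excuse naming a matched-pairs test for a trial without matching.

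**Conclusion.** The point holds in a limited form. The matched-pairs signed-rank test cannot compare two independently randomised arms, and within an arm it measures change under a drug that both arms receive. Kruskal-Wallis can compare the arms, but the text does not tie either test to a comparison.

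The scope is narrow: only continuous secondary outcomes judged non-normal and not rescued by log transformation. The article gives no distribution for any of them, so which ones would fall under the rule is not known. The primary comparison of BMD at 12 months uses ANCOVA and is untouched, as is the sample size. A reader might infer that the main result is at risk, or that the false-positive rate is up to 50%; the documents support neither.

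The illustrative size is disagreement in about 18% to 50% of trials for common changes of 0.3 to 0.9 SD, against 4% to 5% false positives for a rank-sum test. It rests on normal changes, 16 per arm, no true WBV effect, and a misreading that the article does not itself propose.

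**What to change.** Change one sentence in the statistical methods section:

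- For two-arm comparisons of non-normal continuous secondary outcomes, replace the signed-rank test with the Wilcoxon rank-sum (Mann-Whitney) test.
- Keep Kruskal-Wallis for comparing the three groups after the 12-month re-randomisation.
- If the signed-rank test is kept at all, limit it to change within an arm, and state that such results are not used as evidence of a WBV effect.

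Log transformation followed by the t test or ANOVA can stay as it is. The change needs no new data, no extra participants and no revision of the sample size.

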## Discussion

This is a RCT in osteoporotic patients randomized to PTH 1-34 treatment alone or to combined PTH 1-34 treatment and WBV. The primary and secondary endpoints in the study are chosen because previous studies have shown such markers of bone mass, microarchitecture, and turnover, as well as indices of physical performance, to be associated with osteoporosis or fragility fractures.

Earlier studies have reported WBV as a feasible intervention [12] and in older patients the adherence is reported to be good [19].

The intervention is designed to be of long duration (12–24 months) and the setting at the participants’ own home makes the training easy and highly accessible.

The study has limitations including the non-blinded design. It is our hypothesis that the primary endpoint, the BMD as well as a number of secondary endpoints (bone microarchitecture and bone turnover markers) are not at risk of bias by the open-label design. The functional biomarkers on the other hand could be affected by the non-blinded design but the study personnel performing the tests are blinded to the allocation and the baseline data is collected before randomization.

Measurements of quality of life, physical activity, and the FES-I questionnaire are patient-collected data, resulting in the possibility of bias in the reporting.

To limit the possibility of bias by attention, the participants will receive close to an equal amount of contacts by the investigators because of the “at home training design.”.

The study is partially blinded and is protected against selection bias by central randomization after baseline measurements, randomization via web with no stratification, and by allocation concealment.

It is our hypothesis that the DXA, HR-pQCT, and bone marker measurements are not at risk of performance bias. The physical biomarkers may be prone to performance bias, but the test personnel will be blinded to avoid evaluation bias.

To avoid attrition in both arms and ensure adherence, the participants are contacted by telephone each month during the first year and every third month during the second year. The participants receive a direct telephone number and mailing address to the primary investigator and are encouraged to make contact in case of any questions or events.

Every patient is motivated to attend follow-up regardless of randomization or adherence. The participants do not receive payment but are reimbursed for transport expenses.

The adherence to the training protocol is patient reported data and is in risk of reportingbias. A previous study nevertheless found high correlation with the usage of a training logbook to electronic monitoring in the WBV intervention in older adults (overall intraclass correlation coefficient = 0.96), showing a small risk of bias in the collected data on adherence [45].

A combined treatment of WBV and PTH 1-34 might have synergistic or additive beneficial effects on bone strength, thereby reducing fracture risk and making the treatment more cost-effective. A beneficial effect of WBV on muscles, and subsequently fall risk, may lower the fracture risk even further, resulting in comprehensive fracture prevention.

## Trial status

Recruitment of participants started in November 2015 and will be completed in September 2017. This study has been registered at ClinicalTrials.gov (September, 2015: NCT02563353).

## Abbreviations

BMD: Bone mineral density
CTX: Carboxy-terminal type-1 collagen crosslinks
DXA: Dual-energy x-ray absorptiometry
FES-I: Falls Efficacy Scale International
HR-pQCT: High-resolution peripheral quantitative computed tomography
IPAQ: International Physical Activity Questionnaire
P1NP: Procollagen type-1 amino-terminal propeptide
PTH 1-34: Teriparatide
RCT: Randomized controlled trial
SPPB: Short Physical Performance Battery
TUG: Timed Up and Go
WBV: Whole-body vibration
